### Rescue medication

Participants will not be encouraged to receive any other treatment or medication during the study period to prevent any influence on the results. However, in case of deterioration of the condition of AV during the 4-week treatment period and the 24-week follow-up, oral minocycline hydrochloride capsules will be prescribed to the patients (100 mg per day for 7 days) to relieve the symptoms of pain or itching. Details of the medication used will be recorded in the case report form. The proportion of participants using rescue drugs in the groups will be compared.

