**Methods/design:**

One hundred eligible participants with AV will be randomly assigned to an acupuncture or a sham acupuncture group (1:1 allocation). All participants will receive 4-week treatment comprising a total of 12 sessions (3 sessions per week). The primary outcome will be change from baseline in the Skindex-16 scale total score at treatment completion. The secondary outcomes will be Skindex-16 subscale score, Dermatology Life Quality Index scale total score, total lesion count and inflammatory lesion count, visual analogue scale scores for assessment of itch and pain, patient expectations of acupuncture, and blinding of the effect of sham acupuncture. Follow-up evaluation will be performed at weeks 16 and 28. All outcome analyses will be performed in the intention-to-treat population.

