### Sham acupuncture group

Participants in sham acupuncture group will receive sham acupuncture at sham CV14 (10 mm to CV14), LI11 (10 mm to LI11), LI4 (10 mm to LI4), ST36 (25 mm to ST36), and ST44 (10 mm to ST44) with disposable acupuncture needles (0.30 × 25 mm, Huatuo Brand). Sham CV14, LI11, LI4, ST36, and ST44 will be vertically inserted to a depth of 1–2 mm without any manipulation and de-qi. The treatment sessions will last 30 min.

Participants will not be allowed use of other treatments for AV throughout the trial. Detailed information pertaining to use of other treatments will be recorded in the case report form.

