### Secondary outcomes

The change from baseline in the Skindex-16 scale total score at weeks 16 and 28The change from baseline in the Skindex-16 subscale (the symptoms of participants with AV, the emotions of participants with AV, and functioning of participants with AV) scores at weeks 4, 16, and 28The change from baseline in the Dermatology Life Quality Index (DLQI) [29] scale total score at weeks 16 and 28. The DLQI scale is a tool used to assess the health-related QoL of patients with skin diseases. It has a total of ten items. The total score of DLQI ranges from 0 (best) to 30 (worst), with 4 as the MCID in inflammatory skin diseases [30].The change from baseline in the total lesion (inflammatory and noninflammatory lesions) count (TLC) [31, 32] at weeks 4, 16, and 28The change from baseline in the inflammatory lesion count (ILC) [26] at weeks 4, 16, and 28. Inflammatory lesions include inflammatory papules, pustules, and cysts. Noninflammatory lesions include blackhead and whitehead comedones. The lesions are assessed on the forehead, cheeks, nose, and chin. The inflammatory and noninflammatory lesions are counted from the pictures of the face obtained by a dermatologist using a digital camera.The change from baseline in the degree of itch assessed using the Itch Assessment with Visual Analogue Scale (IVAS) [32] at weeks 4, 16, and 28The change from baseline in the severity of pain assessed by visual analogue scale (PVAS) [33] at weeks 4, 16, and 28The participants’ expectations of acupuncture will be assessed at baseline using the following two questions: “Do you think acupuncture will be effective for treating the illness?” and “Do you think acupuncture will be effective for relieving the related symptoms of AV?” The response options will be “yes,” “no,” or “unclear.”

The details of the evaluation of outcomes are shown in Table 1.

**Table 1 Tab1:** Time points for assessment of outcomes

Outcome measures	Enrollment and allocation	Treatment				Follow-up	
	Baseline	Week 1	Week 2	Week 3	Week 4	Week 16	Week 28
Skindex-16 total score	X				X	X	X
Skindex-16 subscales score	X				X	X	X
DLQI total score	X				X	X	X
TLC	X				X	X	X
ILC	X				X	X	X
IVAS score	X				X	X	X
PVAS score	X				X	X	X
Blinding assessment					X		
Expectation	X						
Safety assessment		X	X	X	X		

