### Safety evaluation

Adverse events (AEs), including AEs related to acupuncture (broken needle, local hematoma, infection, abscess, and others), AEs related to postacupuncture (nausea, vomiting, palpitations, dizziness, headache, insomnia, or any other symptoms after acupuncture treatment), and AEs unrelated to treatment will be recorded. For safety assessment, details of all AEs will be recorded by a research assistant in the case report form. Any serious adverse events will be reported within 24 h to the Ethics Approval Committee of the Guang’anmen Hospital of China Academy of Chinese Medical Sciences. The Department of Acupuncture of the Guang’anmen Hospital of China will provide insurance coverage to compensate for any injuries related to the interventions during this study.

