### Quality control

All researchers will take a training course before the beginning of this trial. Due measures will be implemented to ensure the traceability and confidentiality of the case report form, informed consent form, and other original data. A double-input method will be used for data entry. AEs will be recorded in detail, properly handled, and tracked. All trial-related procedures and data management will be supervised. The Data Monitoring Committee of the Guang’anmen Hospital will regularly monitor the recruitment and screening of participants, data collection, monitoring, and verification of AEs to ensure that the study is conducted in accordance with the approved protocol.

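### Scheduled safety assessment stops at week 4, although the trial prescribes oral minocycline as rescue up to week 28

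*Protocol article*

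**What the plan says.** Three parts of the protocol article bear on this.

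- **Rescue medication.** If acne deteriorates, "during the 4-week treatment period and the 24-week follow-up, oral minocycline hydrochloride capsules will be prescribed to the patients", at 100 mg per day for 7 days. About what follows, the section says "Details of the medication used will be recorded in the case report form" and plans to compare the proportion of rescue users between groups.
- **Table 1, under Secondary outcomes.** The row "Safety assessment" is marked at weeks 1, 2, 3 and 4. Its cells at weeks 16 and 28 are blank. The Abstract confirms that these visits exist: "Follow-up evaluation will be performed at weeks 16 and 28".
- **Safety evaluation and Quality control.** The first says "details of all AEs will be recorded by a research assistant in the case report form" and requires serious events to go to the ethics committee within 24 hours. The second says "AEs will be recorded in detail, properly handled, and tracked". Neither gives an end date, and neither names a follow-up visit at which adverse events are asked about.

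**The concern.** The safety schedule covers the needling period and then stops. Exposure to a treatment prescribed by the trial does not stop there: a systemic antibiotic can be given at any time in the following 24 weeks. The article aims to record all adverse events, but after week 4 no scheduled contact asks about them.

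Events that are not asked about are recorded only if the participant volunteers them or is seen for some other reason. Serious events are likely to come to light that way; mild and moderate ones may not. What is at stake is the completeness of non-serious adverse-event data in follow-up, above all after minocycline.

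**Working it through.** The article states no figure to reproduce here. The check compares two schedules, with simple arithmetic.

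**Inputs**
- Treatment period 4 weeks, follow-up 24 weeks, rescue course 7 days (Rescue medication).
- Safety marks at weeks 1, 2, 3 and 4 (Table 1).
- Follow-up visits at weeks 16 and 28 (Abstract; Table 1).

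**Step 1: rescue window against safety schedule.** Rescue can be prescribed until week 4 + 24 = 28. The last scheduled safety assessment is at week 4. That leaves 28 − 4 = 24 weeks with rescue available and no scheduled safety assessment. This is calendar time and not a measure of event risk.

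**Step 2: is the blank an artefact of a broken table?** Table 1 has 10 rows. Seven (Skindex-16 total, Skindex-16 subscales, DLQI, total lesion count, inflammatory lesion count, itch VAS, pain VAS) are marked at both follow-up visits, which makes 7 × 2 = 14 marks. Safety has 0 of 2. The other rows keep their follow-up marks, and the four safety marks fall exactly under the four treatment weeks. The table appears to be read correctly.

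**Step 3: what happens after a rescue course.**

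| | As written | With marks at weeks 16 and 28 |
|---|---|---|
| Scheduled safety assessments after week 4 | 0 | 2 |
| Longest interval without one | 28 − 4 = 24 weeks | 16 − 4 = 12 and 28 − 16 = 12 weeks |
| Course begun after the week 4 visit | no later scheduled assessment | one follows every course begun by the end of week 27 (27 + 1 = 28) |

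**Step 4: how late the added question would come.** A course begun just after week 4 ends at about week 5, which is 16 − 5 = 11 weeks before the week 16 visit. A course begun just after week 16 ends at about week 17, and 28 − 17 = 11 weeks again. The longest recall period is therefore about 11 weeks.

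**Step 5: number of people affected.** The article gives no expected rescue use. If a fraction r of the 100 participants took rescue in follow-up, 100 × r people would be treated with no scheduled adverse-event check afterwards. Each 10 percentage points of use (an assumed unit, not a forecast) means 100 × 0.10 = 10 people. Turning this into missed events would need an event rate and a reporting rate, and the article gives neither.

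**The case against.** The best case for the plan has four parts.

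1. **Nothing is contradicted.** The recording rules are open-ended, they include events unrelated to treatment, serious events are reported within 24 hours, and a data monitoring committee oversees verification of adverse events. This stands. A reader might infer from the blank cells that adverse events in follow-up go unrecorded. The documents do not support that: a reported event can be captured at any time. Only the scheduled enquiry is missing.
2. **Minocycline is a rescue drug and not a trial arm.** Ending scheduled safety assessment when needling ends is coherent for assessing acupuncture, and the row does cover every treatment week. This also stands, but it does not answer for a drug that the trial itself prescribes afterwards.
3. **A journal article condenses the protocol.** Visit procedures and case report form content may sit in a fuller document. That would excuse silence. Here the article states a safety schedule with follow-up columns and leaves those columns empty, so the point rests on what it does state.
4. **The remedy is weak for early courses.** A question up to about 11 weeks after a course depends on memory of minor events. This is correct and limits the gain, though a late question still collects more than no question.

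A reader might also infer that the primary Skindex-16 result, or the comparison of rescue use between groups, is compromised. Nothing here supports that. The primary outcome is measured at week 4, and rescue use is recorded separately from adverse events.

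**Conclusion.** The point holds in a limited form. The stated safety schedule is shorter than the period in which the trial prescribes oral minocycline. Scheduled enquiry about adverse events is absent for the last 24 of 28 weeks, although two visits take place in that time. Non-serious events in follow-up, including those after rescue, may therefore be under-recorded.

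This assumes that Table 1 is the operative schedule and that no unshown procedure adds safety questions at weeks 16 and 28. It also assumes that participants volunteer minor events less fully than they report them when asked. The size of any shortfall cannot be estimated from the article. This is a modest weakness in safety ascertainment that is worth correcting because the remedy is nearly free.

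**What to change.** In Table 1, mark safety assessment at the existing week 16 and week 28 visits. At each, ask about adverse events since the last assessment, and ask specifically about events during or after any minocycline course.

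The cost is two table marks and a few minutes of questions at visits that already take place, with some reliance on recall. Sample size, endpoints and analysis do not change. The article gives the trial's status as not yet recruiting, so on that status the change can be made before enrolment.

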### Outcome measures

The primary outcome will be the change in the total score of the Skindex-16 scale from baseline at the end of 4-week treatment. The Skindex-16 scale is a brief, skin-related QoL scale with satisfactory reliability and validity [20, 21]. It is used to evaluate the efficacy of acupuncture in improving the QoL of patients with AV [20, 21]. The scale includes a total of 16 items that are categorized into three domains: the symptoms of participants with AV, the emotions of participants with AV, and function of participants with AV [20, 21]. The Skindex-16 scale score ranges from 0 (best) to 100 (worst), with a minimal clinically important difference (MCID) as 10 [20, 21].

### Secondary outcomes

The change from baseline in the Skindex-16 scale total score at weeks 16 and 28The change from baseline in the Skindex-16 subscale (the symptoms of participants with AV, the emotions of participants with AV, and functioning of participants with AV) scores at weeks 4, 16, and 28The change from baseline in the Dermatology Life Quality Index (DLQI) [29] scale total score at weeks 16 and 28. The DLQI scale is a tool used to assess the health-related QoL of patients with skin diseases. It has a total of ten items. The total score of DLQI ranges from 0 (best) to 30 (worst), with 4 as the MCID in inflammatory skin diseases [30].The change from baseline in the total lesion (inflammatory and noninflammatory lesions) count (TLC) [31, 32] at weeks 4, 16, and 28The change from baseline in the inflammatory lesion count (ILC) [26] at weeks 4, 16, and 28. Inflammatory lesions include inflammatory papules, pustules, and cysts. Noninflammatory lesions include blackhead and whitehead comedones. The lesions are assessed on the forehead, cheeks, nose, and chin. The inflammatory and noninflammatory lesions are counted from the pictures of the face obtained by a dermatologist using a digital camera.The change from baseline in the degree of itch assessed using the Itch Assessment with Visual Analogue Scale (IVAS) [32] at weeks 4, 16, and 28The change from baseline in the severity of pain assessed by visual analogue scale (PVAS) [33] at weeks 4, 16, and 28The participants’ expectations of acupuncture will be assessed at baseline using the following two questions: “Do you think acupuncture will be effective for treating the illness?” and “Do you think acupuncture will be effective for relieving the related symptoms of AV?” The response options will be “yes,” “no,” or “unclear.”

The details of the evaluation of outcomes are shown in Table 1.

**Table 1 Tab1:** Time points for assessment of outcomes

Outcome measures	Enrollment and allocation	Treatment				Follow-up	
	Baseline	Week 1	Week 2	Week 3	Week 4	Week 16	Week 28
Skindex-16 total score	X				X	X	X
Skindex-16 subscales score	X				X	X	X
DLQI total score	X				X	X	X
TLC	X				X	X	X
ILC	X				X	X	X
IVAS score	X				X	X	X
PVAS score	X				X	X	X
Blinding assessment					X		
Expectation	X						
Safety assessment		X	X	X	X		

*Abbreviations: DLQI* Dermatology Life Quality Index scale, *ILC* Inflammatory lesion count, *IVAS* Itch assessment with visual analogue scale, *PVAS* Pain assessment with visual analogue scale, *TLC* Total lesion count

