### Randomization and allocation concealment

The randomization scheme has been prepared by the National Clinical Drug Testing Institute of the Guang’anmen Hospital. Participants will be randomly assigned to receive acupuncture or sham acupuncture treatment in a 1:1 ratio with the fixed block of 4. Sealed opaque envelopes will be used to ensure randomization concealment. The number of the randomization sequence and information on group allocation will be sealed in ordered envelopes. With the inclusion of patients, those envelopes will be opened one by one in sequence. The envelopes will be kept by a research assistant who is not involved in the treatment or assessment. Additionally, assistant researchers will perform a baseline assessment of all participants (− 1 week to 0 week) prior to randomization.

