### Sample size and statistical analysis

The sample size of this trial was calculated on the basis of primary outcome, which is the change from baseline in the Skindex-16 scale score at the end of week 4. In our unpublished pilot trial, the mean (± standard deviation) reductions in the Skindex-16 scale score after 4-week treatment in the acupuncture and sham acupuncture groups were 12.50 ± 19.09 and 0.40 ± 21.12, respectively. Assuming an alpha risk of 5% and a beta risk of 20%, a sample size of 100 (50 participants in each group) was calculated, considering a 20% dropout rate.

The data will be analyzed using IBM SPSS Statistics version 20.0 software (IBM Corp, Armonk, NY, USA) according to the intention-to-treat principle. Normally distributed continuous variables will be reported as mean ± standard deviation or 95% confidence intervals; non-normally distributed continuous variables will be reported as median (interquartile range). Categorical variables will be presented as frequency (percent). For data pertaining to dropouts, the actual observational value of the last observation will be used for statistical analysis. Between-group differences with respect to normally distributed continuous variables will be assessed using analysis of variance, and those with respect to non-normally distributed continuous variables will be assessed using nonparametric tests for the primary outcome and the secondary outcomes. Data pertaining to the participants’ expectations of acupuncture and the safety evaluation will be analyzed using the chi-square test or Fisher’s exact test. For the blinding assessment, the percentage of participants choosing traditional acupuncture will be assessed using the chi-square test. All *P* values will be two-tailed; *P* < 0.05 will be considered indicative of statistical significance.

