## Discussion

AV is a common chronic inflammatory dermatologic disease. It may affect the physical and mental health of patients and may adversely affect their QoL [34]. According to an epidemiological study, approximately 20% of young people are affected by moderate to severe AV [35]. Several studies have demonstrated a correlation between the QoL and the severity of dermatologic disease [36]. For this reason, this study will only include participants with moderate or severe AV.

The primary outcome of the study will be the Skindex-16 scale score. It is a validated and sensitive scale to measure the QoL of patients with dermatologic diseases [20, 21]. Because lesions of AV mainly occur on areas of the face and are accompanied by other symptoms of itch and pain [32, 33], patients tend to present with psychosocial symptoms and impaired QoL. The Skindex-16 scale consists of 16 questions in the symptoms, emotion, and function domains; responses to each question are scored on a 7-point Likert scale [20, 21]. This scale includes seven questions related to the symptoms (itch or pain) and characteristics (lesions) of AV. It is a sensitive and specific tool to assess the symptoms and QoL of patients with moderate or severe AV. Moreover, we also used the DLQI scale to evaluate QoL. It is a brief, skin-related QoL scale with satisfactory reliability and validity, and it was used to further evaluate the effectiveness of acupuncture in improving the QoL of patients with AV [29]. In addition, TLC, ILC, IVAS, and PVAS will also be used as secondary outcomes to assess the lesion counts and main symptoms (itch or pain) related to AV. These would provide a comprehensive evaluation of the overall effectiveness of acupuncture.

In this trial, we aim to evaluate the therapeutic effect of acupuncture on the symptoms and QoL of patients with moderate or severe AV. The possible placebo effects of acupuncture may be attributable to the participants’ expectations of acupuncture; the degree of trust between the acupuncturist and the participant; and any difference in the type, frequency, or course of the intervention of acupuncture [37, 38]. To partially exclude the placebo effects and demonstrate the real effect of acupuncture, we plan to use sham acupuncture as a comparator.

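### Expectation of acupuncture is recorded before randomisation, yet it is listed as a secondary outcome and given a significance test that cannot be informative

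*Protocol article*

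**What the plan says.** Four parts of the protocol article bear on this.

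- **Status.** The abstract (Methods/design) ends its list of secondary outcomes with "patient expectations of acupuncture, and blinding of the effect of sham acupuncture". The Secondary outcomes section has expectation as its last item.
- **Timing.** That item reads, of the participants, "expectations of acupuncture will be assessed at baseline using the following two questions". Each question has three possible answers (yes, no, unclear). Table 1 marks expectation once, in the Baseline column. Under Randomization and allocation concealment, "assistant researchers will perform a baseline assessment of all participants", in the window ending "1 week to 0 week) prior to randomization".
- **Analysis.** Under Sample size and statistical analysis, data on participants' "expectations of acupuncture and the safety evaluation will be analyzed using the chi-square test" or Fisher's exact test. All P values are two-tailed, with significance at 0.05. The article gives no other analysis of expectation.
- **Primary outcome.** The same section assesses normally distributed continuous variables, including the week-4 change in Skindex-16 total score, by analysis of variance. It names no baseline covariate.

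**The concern.** An outcome is something that allocation could change. An answer given before allocation cannot be one, however relevant it may be to how patients respond. The blinding question, listed beside it in the abstract, is different: it is asked in week 4, after treatment, so the arms can genuinely differ on it.

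Listing expectation as a secondary outcome and attaching a P value invites two wrong readings in the final report. A small P value may be taken as a finding about the arms. A large one may be taken as proof that the arms were alike in expectation. The test supports neither. What is at stake is clear reporting of a secondary item, not the efficacy conclusion.

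**Working it through.** The plan states no figure for this item, so there is none to reproduce. The check has four steps.

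**1. Timing against status.** Expectation is measured at baseline only (Secondary outcomes; Table 1). Baseline precedes randomisation (Randomization and allocation concealment). It is classed as a secondary outcome (abstract; Secondary outcomes). The first two statements rule out the third. If randomisation works, the null hypothesis of a between-arm test is true by design.

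**2. What the test would return.** The planned 2 × 3 chi-square test was simulated on answers fixed before allocation: 100 participants, 1:1, blocks of 4, 20,000 replicates. The answer shares are assumed.

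| Assumed yes / no / unclear | Rejection rate at nominal 0.05 |
|---|---|
| 60 / 10 / 30% | 0.051 |
| 40 / 20 / 40% | 0.052 |
| 80 / 5 / 15% | 0.041 |

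The test rejects at about its nominal rate and carries no other information. For two questions:

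- If the answers were independent, the chance of at least one rejection is 1 − 0.95² = 0.0975.
- If the answers to the two questions were identical, it is 0.05.

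The questions are similar (effect on the illness; effect on its symptoms), so the true value lies between about 5% and 10%.

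**3. Why non-significance does not show balance.** Simplify to the proportion answering yes, with 50 per arm. The standard deviation of the chance difference is √(p(1 − p) × 2/50).

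- p = 0.5: √(0.25 × 0.04) = 0.100
- p = 0.7: √(0.21 × 0.04) = 0.092

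A difference must exceed about 1.96 × 0.100 = 0.196, or 1.96 × 0.092 = 0.180, to reach P < 0.05. An imbalance of 15 percentage points would pass as non-significant.

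**4. Baseline adjustment of the primary outcome.** The inputs are the pilot standard deviations in the Background (21 per arm).

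- Week-4 score, 15.40 and 19.39: pooled √((15.40² + 19.39²)/2) = √306.57 = 17.51
- Change from baseline, 19.09 and 21.12: pooled √((19.09² + 21.12²)/2) = √405.24 = 20.13

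A model of the week-4 score adjusted for baseline estimates the slope b that minimises the within-arm variance of (week-4 score − b × baseline). Analysing change fixes b = 1, and analysing the week-4 score alone fixes b = 0. The adjusted residual SD can therefore be no larger than the smaller of the two, 17.51, apart from one degree of freedom spent on the slope.

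- Ratio of standard errors: at most 17.51/20.13 = 0.870, a reduction of at least about 13%
- With 50 per arm: 20.13 × √(2/50) = 4.03 points, against at most 17.51 × √(2/50) = 3.50 points

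**The case against.** The strongest reply is that this is a labelling slip in a journal article. The text and Table 1 both say openly that expectation is a baseline item, so few readers would credit a difference to treatment. The statistics sentence does not literally say that expectation is compared between arms. An unseen analysis plan may treat the variable properly. No efficacy conclusion depends on it.

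Most of this stands and sets the severity. The between-arm reading is an inference, though a natural one: the same sentence covers the safety data, and it follows the sentence on between-group differences. A further analysis elsewhere would not undo the classification or the test, both of which the article states.

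Four stronger readings are tempting, and the document does not support them.

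- *The expectation test was meant to measure placebo effects and fails to.* The Discussion does say "The possible placebo effects of acupuncture may be attributable to the" expectations, but among other factors and without calling expectation the main one. It gives the task of handling placebo effects to the control arm: "To partially exclude the placebo effects and demonstrate the real effect of acupuncture, we plan to use sham acupuncture as a comparator". The article claims nothing for the test in this respect.
- *Any significant result must be chance.* That holds only if allocation and concealment work. A difference could also come from failed randomisation, although a baseline test is a poor detector of that.
- *A known prognostic variable is being wasted.* Nothing in the document shows that expectation predicts Skindex-16 change. If a correlation of 0.2 to 0.4 is assumed, adjusting for it cuts the standard error by 1 − √(1 − r²), that is 2.0% to 8.3%.
- *The plan is at fault for lacking an expectation covariate or interaction.* Such detail is commonly left to the full protocol or analysis plan.

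**Conclusion.** The point holds, and it is minor. A variable measured before randomisation is classed as a secondary outcome, and its one stated analysis is in effect a baseline significance test. That test can reveal only chance or failed randomisation, and it cannot establish balance. The spurious-result rate of about 5% to 10% assumes that each question is tested between arms at 5%.

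The gain of at least about 13% from baseline adjustment rests on three assumptions: the pilot standard deviations carry over to this trial; they come from only 21 participants per arm and so are imprecise; and the stated analysis of variance has no baseline covariate, as the article reads. It is an improvement to make in the same edit, not evidence that the stated primary analysis is invalid.

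**What to change.** 1. In the abstract and under Secondary outcomes, remove expectation from the secondary outcomes. Add it to the baseline characteristics under Study recruitment, and keep its row in Table 1 marked as a baseline characteristic.
2. Under Sample size and statistical analysis, drop the significance test for expectation. State that the answers to each question will be tabulated by arm as counts and percentages.
3. In the same section, replace the unadjusted analysis of variance for the primary outcome with a linear model of the week-4 Skindex-16 total score (or its change, which gives the same treatment estimate) on arm and baseline score, reporting the adjusted difference with its 95% confidence interval.
4. Optional: if the investigators want expectation as a covariate or an exploratory effect modifier, state beforehand which of the two questions is used and how its three answers are coded. An interaction estimate would be imprecise with 100 participants.

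The cost is wording only. No new data are needed, because baseline Skindex-16 and expectation are already collected, and the Trial status section reports no recruitment yet.
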